## Abstract

**Introduction:**

The minimally conscious state (MCS) is one of the common and serious complications of stroke patients. Its incidence is higher than that of other types of consciousness disorders. The prolonged monitoring and comprehensive management of patients with MCS imposes substantial socioeconomic burden, creating multifaceted challenges for healthcare systems and considerable strain on familial resources. However, there are still few studies on the treatment of MCS, so there is a lack of standardized and effective treatment for MCS, which needs to be solved urgently. In order to solve this problem, this study proposes a treatment plan of acupuncture for arousal combined with repetitive transcranial magnetic stimulation (rTMS). Acupuncture for arousal is a clinical acupuncture therapy. Accumulating evidence from the published literature indicates that acupuncture for arousal interventions can significantly enhance consciousness levels in comatose patients. Nevertheless, conventional acupuncture monotherapy necessitates extended treatment durations, potentially compromising patient outcomes and neurological recovery trajectories. rTMS can excite or inhibit specific cortical functional areas of the brain, thereby improving the level of consciousness in comatose patients. The significance of this study is to clarify the efficacy and safety of wake-promoting acupuncture combined with repetitive transcranial magnetic stimulation in patients with minimal consciousness after stroke, and to add a standardized and effective scheme for the treatment of MCS. Furthermore, this investigation employs neural-specific biomarkers and functional magnetic resonance imaging to elucidate the mechanisms underlying regional brain functional reorganization. These neuroimaging and molecular approaches may establish a robust scientific foundation for future investigations into consciousness-restoring mechanisms in patients with MCS.

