Compared with other states of disturbance of consciousness after stroke, the incidence of MCS after stroke is high, and patients often need long-term monitoring and treatment to survive, causing great burden and huge economic pressure to society and families (23). In addition, there is no effective and standardized treatment for MCS, so it is of great economic and social significance to find a safe and effective wake-up method for MCS patients. Lam Ching et al. (24) reported that compared with Western medicine, acupuncture alone or plus rTMS, traditional Chinese medicine, traditional Chinese medicine combined with Western medicine were more effective in improving depression symptoms of patients with post-stroke depression. Among all therapeutic strategies evaluated, the combination of acupuncture with rTMS emerged as the most efficacious intervention modality, suggesting potential synergistic neuromodulatory mechanisms warranting further investigation in controlled clinical trials. Therefore, for patients with post-stroke disturbance of consciousness, we put forward the scientific hypothesis that acupuncture combined with rTMS can promote the improvement of consciousness in patients with MCS. This study will utilize acupuncture for arousal combined with rTMS to treat post-stroke MCS, conducting efficacy and safety evaluations to facilitate its future clinical application and to establish a standardized, effective treatment scheme for MCS. Meanwhile, through the detection of neural specific markers and brain functional magnetic resonance imaging, the mechanism of promoting the functional reorganization of brain regions will be discussed, which could provide a more scientific basis for the study of the wake-promoting mechanism of MCS in the future.

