### Sample size calculation

The GCS score was used as the primary outcome measure for the sample size calculation, following the method outlined by Lai Shilong in the Methodology of Clinical Research of Integrated Chinese and Western Medicine. Based on a study by Li Yuyuan et al. (25), the GCS score for the acupuncture combined with rTMS group was 10.30 ± 3.47 after 4 weeks of treatment. The GCS score for the acupuncture-only group was 8.33 ± 2.97, whereas that for the rTMS group was 8.16 ± 2.98. Taking *α* = 0.05, two-sided test, and *β* = 0.2, the ratio of the three groups of sample sizes was 1:1:1. After the above values are substituted with PASS 15 software, the sample size required for each group is calculated to be 32 cases. Considering a shedding rate of 20%, 39 patients are included in each group, and 117 patients are ultimately included in this study.

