#### MRI data analysis

The MRI data are preprocessed using the SPM8 software platform (SPM8, Wellcome Department of Imaging Neuroscience, London, United Kingdom). Referring to the study of resting-state connectivity of DLPFC in PSD patients (32), we select DLPFC as the seed point, use WFU Pickatlas (33) to define the region of interest (ROI) in CCN, and perform whole brain regression analysis. The resting state connectivity of DLPFC in CCN is compared among the three groups, and the brain changes of each group are evaluated by paired t-test through intra-group analysis (before and after treatment). Covariates such as age and gender are included in the data analysis. The Pearson correlation coefficient is used to analyze the relationship between the improvement of the scale and the change of fMRI image data.

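### The planned Pearson correlation of scale improvement with fMRI change names no treatment-arm term; if it is pooled over arms, arm differences alone can produce a weak correlation

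*Protocol article*

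**What the plan says.** The protocol article's section on MRI data analysis describes three steps. Connectivity of the dorsolateral prefrontal cortex (DLPFC) is compared among the three groups. Within groups, "the brain changes of each group are evaluated by paired t-test through intra-group analysis (before and after treatment". Finally, "The Pearson correlation coefficient is used to analyze the relationship between the improvement of the scale and the change of fMRI image data".

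The only adjustment mentioned is general: "Covariates such as age and gender are included in the data analysis". Arm is not among the covariates named, and a plain Pearson coefficient takes no covariates.

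The imaging serves a declared mechanism aim. The abstract says that biomarkers and fMRI are used "to elucidate the mechanisms underlying regional brain functional reorganization", and the main Introduction says that through them "the mechanism of promoting the functional reorganization of brain regions will be discussed". The trial's hypothesis is that "acupuncture combined with rTMS can promote the improvement of consciousness in patients with MCS", so arm differences in the scales are what it sets out to find.

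**The concern.** Each patient contributes one scale change and one fMRI change. A coefficient computed over all patients has two sources: association between patients inside each arm, and the way the arm means line up. Only the first adds evidence that recovery goes with connectivity change beyond the fact that the arms differ. The second restates the treatment effects on the two variables.

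The conditions for this are close to the trial's own expectations. It hypothesises an arm effect on consciousness and tests for one on connectivity. Two of the three arms receive rTMS over the DLPFC, which is also the fMRI seed region, so an arm effect on connectivity is plausible.

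At stake is the mechanism argument. This correlation is the only analysis in the article that links imaging change to change on the scales.

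**Working it through.** **Plan's own figure.** The article gives no figure for the correlation. The sample size serves only to set N: 32 per group (N = 96) before the dropout allowance and 39 per group (N = 117) after it. A one-way ANOVA calculation on the three planning means, with a common SD of 2.97 to 3.0, reproduces 32.

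**Inputs from Sample size calculation.** For the combined arm, "the GCS score for the acupuncture combined with rTMS group was 10.30 ± 3.47 after 4 weeks of treatment". Values for both single-treatment arms appear in the same section: "The GCS score for the acupuncture-only group was 8.33 ± 2.97, whereas that for the rTMS group was 8.16 ± 2.98". These are post-treatment scores; the SD of change is not given, so they stand in for improvement.

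**Assumed inputs.** The arm effect on fMRI change (not in the article), and zero scale–fMRI correlation inside every arm.

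**Step 1: planned arm effect on the scale.**
- Grand mean = (10.30 + 8.33 + 8.16)/3 = 8.93; deviations 1.37, −0.60, −0.77.
- Between-arm variance = (1.8769 + 0.3600 + 0.5929)/3 = 0.943.
- Mean within-arm variance = (3.47² + 2.97² + 2.98²)/3 = 9.914, so SD = 3.15.
- f² = 0.943/9.914 = 0.0951, f = 0.308; share of variance due to arm = 0.0951/1.0951 = 0.087.

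**Step 2: correlation induced by arm means alone.** If the arm effect on fMRI has the same pattern and is k times as large in SD units,

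r = k f² / √[(1 + f²)(1 + k² f²)].

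For k = 1, r = 0.0951/1.0951 = 0.087. For k = 2, r = 0.1903/√(1.0951 × 1.3806) = 0.155.

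**Step 3: rejection rate at k = 1.** By Fisher's z, atanh(0.087) ≈ 0.0871.
- N = 117: 0.0871 × √114 = 0.93, so Φ(0.93 − 1.96) + Φ(−0.93 − 1.96) ≈ 0.15.
- N = 96: 0.0871 × √93 = 0.84, so Φ(0.84 − 1.96) + Φ(−0.84 − 1.96) ≈ 0.13.

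The critical |r| is 0.182 at N = 117 and 0.201 at N = 96, so the average spurious r is well below significance.

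**Step 4: simulation with the same pattern, 20,000 trials per scenario.**

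| fMRI arm effect relative to planned GCS effect | mean pooled r | rejects, N = 96 | rejects, N = 117 |
|---|---|---|---|
| 0 | 0.00 | 5% | 5% |
| 0.5 | 0.05 | 7.0% | 7.8% |
| 1 | 0.087 | 13.2% | 15.1% |
| 1.5 | 0.124 | 22.5% | 26.3% |
| 2 | 0.155 | 33% | 39% |
| 3 | 0.20 | 51% | 59% |

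With arm means removed (N − 4 degrees of freedom), mean r is about 0 and the rejection rate is 4.7% to 5.4% throughout.

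**Step 5: other assumed patterns, N = 117.** Shifts are in SD units, in the order acupuncture / rTMS / combined; 6,000 trials per scenario, with a 10,000-trial repeat in brackets.
- 0/0/0.63: 14.9% (14.4%)
- 0/0/1.0: 26.6% (27.0%)
- 0/0.5/1.0: 17.2% (16.4%)
- 0/1/1: 8.9% (9.2%)
- 0/1/1.5: 22.2% (21.7%)

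Hand check for 0/0/0.63: the fMRI deviations are −0.21, −0.21, 0.42. Between-arm covariance = (1.37 × 0.42 + 0.60 × 0.21 + 0.77 × 0.21)/3 = 0.288, and r = 0.288/√(10.857 × 1.088) = 0.084. At 32 per arm the same five patterns give 7.7% to 22.7%. The size depends on how closely the two patterns of arm means line up, which is why 0/1/1 gives the least.

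**The case against.** The strongest reply is that pooling is inferred. The correlation sentence follows closely on text about analysis within groups, and separate coefficients per arm would satisfy it and be free of the problem. A condensed article may also leave the adjustment set to a fuller document, and the covariate list is open-ended. This stands in part. A reader might infer that the article commits to ignoring arm; it does not. But it does fix a method, a plain Pearson coefficient, and it attaches group wording to the other two steps and not to this one. The sentence therefore needs settling.

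Second, if treatment moves both variables, the marginal correlation is truly non-zero, and rejecting zero is then correct for that quantity. This also stands. The test's type I error is not broken. The rates above are errors only about within-arm association, which is the part that adds to a mechanism argument.

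Third, the inputs are soft: no fMRI effect is given, the GCS figures are not changes, and the scale to be correlated is not named and could be the CRS-R. This is accepted, and it is why a range is shown.

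A reader might also infer that Pearson is wrong because the scales are ordinal. With totals running from 0 to 23 on the CRS-R that is a preference, and no error follows from it here.

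**Conclusion.** The point holds as a minor, conditional one. It needs the coefficient to be pooled over arms, and arm effects on both scale improvement and fMRI change whose patterns line up at least in part. At an fMRI effect equal to the planned GCS effect, the spurious correlation is about 0.09 and the rejection rate 13% to 15% in place of 5%. The other assumed patterns give about 9% to 27% at N = 117. With no fMRI arm effect there is no inflation.

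A reader might infer that a false mechanism finding is near certain, or that the efficacy results are compromised. Neither is supported. Rates above one half arise only with an assumed fMRI effect about three times the planned GCS effect, or with both effects enlarged well beyond the planning values. The randomised comparisons of scales and connectivity do not use this coefficient. The article also plans comparisons of connectivity among and within groups, so the mechanism aim does not rest on the correlation alone.

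**What to change.** In MRI data analysis, replace the plain Pearson coefficient with one of two equivalent forms: a partial correlation between scale improvement and fMRI change adjusted for arm, or a linear regression of scale improvement on fMRI change with arm in the model. Either can carry the age and gender covariates already named. Name the scale, show the coefficient within each arm, and state that an unadjusted pooled coefficient will not be used as evidence of mechanism.

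Arm costs two degrees of freedom (115 to 113 at N = 117), plus one if the baseline score is added. The change is a sentence or two of text, with no effect on data collection, sample size or trial conduct. The per-arm coefficients should be read as descriptive: with 39 patients the critical |r| is 2.026/√(2.026² + 37) = 0.32.

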### Patient and public involvement

This study protocol does not incorporate patient or public involvement in the design, implementation, or selection of outcome measures. Assessment of intervention burden from the patient perspective will not be conducted within the scope of this investigation. The results of this study will be disseminated to study participants via our hospital’s website.

### Ethics and dissemination

The Ethics Committee of the Second Chinese Medicine Hospital of Guangdong Province believes that this study is in line with the principles of the “Helsinki Declaration” and meets the requirements of medical ethics. The study was successfully reviewed by the hospital ethics committee (Research Ethics Review Approval Number: K202405-003-01). In addition, this study was registered on the Chinese Clinical Trial Registry (CHICTR) platform. (Clinical Trial Registration Number: ChiCTR2400086163.) In this study, each patient will be provided with sufficient information about the purpose of the study, possible risks, and benefits. Before enrollment, the informed consent documentation will be thoroughly explained to patients’ legal representative by the investigator, after which authorized family members will sign written informed consent in accordance with institutional ethics requirements. After the completion of the trial, the statistical results will be made public and published in peer-reviewed journals.

## Discussion

According to global epidemiological surveys (23, 34), stroke is the second leading cause of disability and death worldwide, and stroke has grown to be the leading cause of death from disease in China with an increasing incidence in younger populations (35). The MCS is a serious poststroke disturbance of consciousness. It refers to the patient’s ability to retain a part of consciousness and attention to the outside world and himself, with a clear but limited, tiny cognitive self and the surrounding environment. The emergence of MCS signifies a positive prognostic development, bringing hope for more patients with disturbance of consciousness to continue treatment. This single-center design, third-party, blinded, randomized controlled trial will test the curative effect of the acupuncture for arousal combined with rTMS and provide a more clinical basis for the awakening treatment of disturbance of consciousness in the future.

According to the theory of traditional Chinese medicine, stroke is located in the brain. Acupuncture for arousal improves the level of consciousness by acupuncture at the head and neck acupoints. The acupoints selected by the acupuncture for arousal are located in the Governor Vessel (GV), the Gallbladder Meridian of Foot Shaoyang (GB), and the Bladder Meridian of Foot Taiyang (BL), which are the key parts of the meridian circulation in the brain. This is in line with the principle that “where the meridian passes, the main points reach.” The selected acupoints are bilateral GB20 (Fengchi), GB12 (Wangu), BL10 (Tianzhu), GV15 (Yamen), and GV16 (Fengfu). Among them, GB20 can promote the blood circulation of peripheral nerve blood vessels, increase the blood flow rate, relieve vasospasm, and improve the level of ischemia and hypoxia in brain cells (36). Research has shown that acupuncture at GB12 can improve the blood supply of the vertebral–basilar artery and promote the formation of cerebral collateral circulation (37, 38). BL10 can regulate the qi and blood of the head meridians and regulate the function of the cerebral cortex (39). GV15 and GV16 are selected for the Governor Vessel, which dredges the governor vessel and regulates spirit, opening the orifices. After acupuncture, it can promote the activity of the plasma fibrinolytic system, which is beneficial for the dissolution and absorption of blood clots in cerebral hemorrhages and promotes the recovery of comatose patients (40, 41). Furthermore, rTMS is a clinically recognized physical wake-up treatment. Its therapeutic target is in a specific cortical functional area, which can activate or inhibit the activity of cortical–cortical and cortical–subcortical neural networks (17) and regulate the plasticity of the cortex (42), thereby achieving perceptual remodeling. The pathological mechanism of stroke is related to the activity of the *α*-amino-3-hydroxy-5-methyl-4-isoxazole propionate (AMPA) receptor. AMPA receptor is a glutamate receptor that mediates rapid excitatory synaptic transmission in the central nervous system. It is involved in synaptic plasticity and is closely related to neural development, learning and memory (43). However, its excessive activation has a strong excitatory toxicity. rTMS may play a role by inhibiting the over-expression of AMPA receptor (44).

Acupuncture is still based on a summary of clinical experience, and there are various problems in research design. Because coma patients cannot sit autonomously, traditional acupuncture treatment generally involves patients in the supine position. Owing to their position, fewer neck acupoints are selected. This study selects head and neck acupoints and innovatively selects the acupuncture position in which the head of the patient is fixed by a nursing worker or family member to maintain the sitting position. In the previous clinical trial, this study found that acupuncture at neck acupoints can improve the blood supply of the vertebral artery and carotid artery, and the neck acupoints selected by this acupuncture method are close to the medulla oblongata and brainstem reticular structure. Acupuncture may improve the signal of the brainstem reticular ascending activation system, improve the blood supply of the brain, and enhance the compensatory mechanism of the brain. In addition, a sitting position can induce the emergence of proprioception in patients, which can achieve a better curative effect. In addition to the use of the most common behavioral assessment scale, such as the GCS, this study also adds the CRS-R score to accurately determine the level of minimum consciousness and combines objective-specific neurological function laboratory indicators to improve the objectivity and accuracy of the assessment. A follow-up at 4 weeks after the end of treatment will be added to verify that the study had long-term efficacy. NSE and S-100B are specific markers of the central nervous system. Clinical studies have demonstrated elevated NSE levels in both cerebrospinal fluid and peripheral blood shortly after stroke onset (45, 46),while increased S-100B protein concentrations have been consistently observed in cerebrospinal fluid of stroke patients (47, 48). And the degree of cognitive dysfunction in stroke patients is positively correlated with the expression of NSE and S-100B (49). Xu et al. (50) have also confirmed that the expression of NSE and S-100B in the serum of stroke patients is up-regulated after stroke, and the expression is down-regulated after treatment, reflecting that NSE and S-100B can help determine the prognosis of stroke. Therefore, NSE and S-100B will be used as one of the outcome indicators to help verify whether this study has therapeutic significance through the values changes before and after treatment. A reduction in post-treatment NSE and S-100B levels compared to baseline values will indicate therapeutic significance. Brain functional magnetic resonance imaging is an advanced brain function examination tool that can be accurately positioned clinically. BOLD-fMRI reflects neural activity by detecting changes in blood oxygen in the brain, and provides a visual research method for studying changes in brain function (51). However, in the current research on the brain effect of acupuncture based on BOLD-fMRI, Taixi (KI3), Hegu (LI4) and other limb acupoints are the most studied acupoints (52, 53). This study will select head and neck acupoints and use BOLD-fMRI to observe the brain effects during acupuncture objectively and stereoscopically, so as to improve the evaluation of the efficacy of patients with MCS, and further explore the mechanism of functional reorganization of brain regions in MCS patients.

However, this study also has several limitations. First, owing to ethical principles, the basic Western medicine treatment of patients still needs to be carried out at the same time, and its impact on efficacy cannot be ruled out, which may affect the evaluation of overall efficacy. But this study also avoids the use of awakening drugs that affect neurological function and drugs that affect brain metabolism as strictly as possible. For example, citicoline can improve cognition by reducing oxidative stress and increasing antioxidant capacity (54). Trimetazidine improves brain activity by improving brain glucose uptake, anti-oxidation and regulating AMPA metabolism (55). Second, efficacy assessment employs a third-party blind evaluation methodology conducted by professionally trained evaluators. While these evaluators remain unaware of treatment group assignments and are not involved in the intervention delivery, we acknowledge that some element of subjectivity may persist in the assessment process despite these methodological safeguards. In addition, the acupoints selected in this study are in the neck, and electrical stimulation treatment is performed. The general acupuncture needles and electroacupuncture stimulators cannot enter the magnetic resonance machine room, so it is impossible to perform a BOLD-fMRI examination at the same time. Moreover, the data processing of fMRI mainly focuses on the analysis of the dorsolateral prefrontal lobe. In the future, research on other related brain regions can be expanded further to explore the mechanism of functional reorganization of brain regions. Therefore, in future research, we should actively apply for more funds, optimize the experimental design scheme, and improve the imaging examination skills to supplement this research. Finally, since this study is a single-center study conducted only in the Second Chinese Medicine Hospital of Guangdong Province, the results of our study may have limitations: while our enrolled patient population represents the demographic profile and disease spectrum typically encountered in our locale, these characteristics may not fully reflect patient populations in other geographic regions. Additionally, despite our development of detailed procedural guidelines to enhance methodological reproducibility, potential variations in technical execution of TCM interventions cannot be entirely eliminated. However, it cannot be denied that the single-center design has advantages in controlling variables and ensuring treatment consistency. Therefore, even with these limitations, this study provides valuable evidence for the feasibility of acupuncture for arousal combined with rTMS in the treatment of MCS patients, and provides more experience for future research in this field. In future studies, we hope to carry out multi-center randomized controlled trials in a number of hospitals in different regions (including Western hospitals) to verify the broad applicability of our research results.
